### Educational intervention, theoretical background and program

We based the educational intervention on the concept of nutrition-specific HL, referred to as food literacy (FL), as suggested and described by Krause et al. [57]. The three functional, interactive, and critical forms of HL/FL [57–59] were to play a key role in the various stages of the dynamic Health Action Process Approach (HAPA) [60], which provided the underlying model to explain behavior change. We hypothesized that becoming more food literate will empower and motivate participants to change their individual eating behavior and actively involve their community of work colleagues, family, and friends when eating more healthily, thereby lowering their Na intake at the workplace and at home.

The education program was structured in five themed workshops, which were combined with intermediate email messages providing additional information, links to online nutrition games or films, and practical assignments (Fig. 1). Thus, continuous contact with participants was possible over the one-year intervention period, as recommended by Schwarzer [61]. Multicomponent interventions combining web-based components with in-person contact also have been shown to be effective [62, 63]. The program imparted knowledge on balanced diet and health, with a specific focus on salt as a dietary risk factor, and fostered practical abilities and skills related to food choice in and out of the home. Prior to the final workshop on program sustainability, participants completed an online, program-specific evaluation questionnaire (Fig. 1). Two experienced nutritionists who are registered dieticians and lecturers in dietetics realized the education program [64].

A description about development and implementation of the environmental and educational intervention will be published elsewhere.

### Data collection at cluster level

#### Catering survey

After registration, catering production managers completed a 57-item questionnaire [36] that served to characterize catering facilities by operational factors, offerings, and health promotion interests and activities. They also completed a quality evaluation checklist, rating the actual catering offerings in comparison with the SQSCC [36, 65]. The information helped the coach to understand specific organizational conditions and prepare the intervention activities.

Three short questionnaires were established and applied to follow up on the guideline compliance dimensions that were targeted by the environmental program (Fig. 1) [66]: (1) the awareness of catering staff of the SQSCC and salt-health issues at t0; (2) their intermediate attitude and motivation towards implementing planed changes and continue intervention measures in agreement with the standards (t3), and (3) to evaluate the environmental program and coaching overall at t12.

#### Intervention actions and food sampling

The intervention focused on lunch as the main meal most commonly consumed in business staff restaurants, and the most frequently purchased and consumed offerings. These were different types of plated, multicomponent menus such as meat or fish, daily special, vegetarian, etc., which could be supplemented by a soup or menu salad [18]. We chose a stepwise improvement process, planning targeted changes in food production per menu component, which typically were (1) a nondairy meat, fish, or plant protein component; (2) a carbohydrate, starchy foods component; and (3) a vegetable or menu salad component. These components were either presented separately on a plate or as part of a composite dish (e.g., lasagna). Supplementary components on a different food base included (4) gravy/sauces and (5) dairy products like grated cheese or any other kind of topping. The different plated menus as well as self-service, buffet-style offerings would thus be broadly affected by Na/NaCl reduction measures. Actions taken to reduce Na/NaCl could involve the entire operating sequence that is menu-planning, purchase/use of specific products, recipes, production, serving procedures, and more.

Food sampling at five times (t0 to t12) included all individually produced components of plated menus offered on sampling dates. Depending on the implemented intervention actions, additional food samples may have been taken. Single food items were sampled as end products prior to serving, in specifically labeled containers to allow identification of organization, follow-up date, type or name of food, and menu source. Standard serving size was determined by weighing servings set by restaurant managers and served by staff. For all buffet-style and additional food items without fixed serving sizes, reference values were used from the food record checklist (see below, data collection at participant level). Sales numbers of the food items were recorded on each day food was sampled.

#### Laboratory analysis of sodium and potassium concentrations in food

Study staff delivered catering food samples in labeled containers on the day of production to Federal Food Safety and Veterinary Office (FSVO) laboratories. Upon delivery, the samples were homogenized using a laboratory mixer and, depending on day of analysis, were kept cooled (4 °C) or deep-frozen (− 20 °C). The study lab technician weighed duplicate portions of the food samples for Na and K extraction with 1% nitic acid (at 90 °C) and subsequent analysis; approximately 40 g were retained deep-frozen for repeat or additional measurements. Na and K (mg/kg of fresh mass) were determined through inductively coupled plasma optical emission spectrometry (ICP-OES; 589.5 nm Na; 766.4 nm K; iCAP 7400 dual view, Thermo). The accuracy and precision of the ICP-OES determinations were checked periodically with National Institute of Standards and Technology (Gaithersburg, MD, USA) standard reference material SRM1548a-Typical Diet. The measurements of Na and K values in the reference material agreed well with the certified values. For additional, independent quality control and evaluation purposes, FSVO laboratories used an argentometric method to determine chloride (Cl) in 24 selected menu components that were uniformly distributed over the concentration range. Linear regression analysis of Cl vs. Na (R^2^ = 0.98) showed that the 95% confidence interval of the slope included the theoretical Cl/Na atomic weight ratio of 1.54, which indicated that Na and Cl content were correlated and Na therefore well represents NaCl content.

#### Estimation of sodium and potassium content of menu components and servings

Na and K concentrations of menu components in mg/kg were converted to g per 100 g (%) and to g per serving. The equivalent NaCl content was calculated by multiplying Na content by 2.54, the molar weight ratio of NaCl (58.5 mg/mmol) to Na (23 mg/mmol). Data for served menu components were added to represent the overall Na/NaCl and K contents of specific served, plated menus. Serving sizes, Na, NaCl, and K contents were weighted by menu sales numbers to understand the respective impact upon employees’ intakes.

### Data collection at participant level

#### Health questionnaire

Participants as well as nonresponders filled out a health questionnaire comprised of 68 questions at t0, and participants did so again at t12. The questionnaire assisted characterization of study participants and nonresponders, and captured changes in secondary outcome measures and specific items related to the education program. It covered seven areas: demographic and socioeconomic position, health status, health in everyday life, and the health behaviors eating and drinking, physical activity, and smoking. It was largely based on existing, validated questionnaires to allow for data comparability with other international surveys [66]. Core questions inquired about generic HL and nutrition-specific HL/FL, salt awareness, and nutrition self-efficacy. Given the workplace health promotion setting of our trial, we restricted assessment of generic HL to the set of items under the health promotion domain of the validated European Health Literacy questionnaire (HLS-EU-Q47, in German) [67, 68], and calculated the HL index (0 to 50 points) according to the HLS-EU Consortium recommendation [69]. HL was categorized as inadequate (25 or less), problematic (> 25–33), sufficient (> 33–42), and excellent (> 42–50). For measurement of nutrition-specific HL/FL, we integrated a set of 16 items in the questionnaire, which underwent two-stage testing [70]. Validation [71] revealed 12 of the items suitable to reliably represent basic elements of FL and form a practical short questionnaire (SFLQ) for which a FL score (7–52, lower score for lower FL) was established.

The questionnaire could be completed in paper form or filled in online. Study staff checked the returned/submitted questionnaires for completeness and inconsistencies, and followed up with participants to obtain missing answers.

#### Health assessments

As shown in Fig. 1, participants from organizations in both study arms were followed-up at their workplaces every three months, from t0 to t12. In a short follow-up of 20 min per participant, three experienced and trained dieticians/nutritionists instructed participants about urine collection, handed out study materials, and used portable calibrated instruments to obtain body weight, height, waist and hip circumference, blood pressure, and heart rate measurements. As of t3, and in accordance with ethical guidelines, participants were asked to report any adverse events relating to study participation. Measurements were recorded on result sheets that were given to participants for personal information after data entry into the trial database.

#### Sodium, potassium, and iodine intake measurements

We repeated a three-day measurement protocol to estimate Na, K, and I intakes during the one-year intervention period. The protocol combined 24-h and spot urinary excretion with questionnaire measures as suggested elsewhere [72, 73]. Because 24 h of urine mostly reflects nutrient intake one to two days prior to collection, we applied a Na- and K-specific food record checklist (FRCL) on days one to three to complement collection of a spot-urine on day two, and a 24-h urine collection on day three. We were aware of the burden of repeated 24-h urine collections, and the related risk of dropouts, and therefore we requested all participants to collect urine for 24 h at t0 and t12, but only a 15% random sample to collect 24-h urine at t3, t6, and t9. Everyone had to complete the FRCL and provide spot urine collections, though.

#### Food record checklist

A semi-quantitative Na- and K-specific FRCL was filled out on three previously agreed on, consecutive days to complement collection of spot- and 24-h urine with qualitative information on Na and K food sources and their daily consumption frequency, discretionary salt use at time of eating, and food/menu choices and sensory rating in the staff canteen. This dietary assessment instrument [74] was newly developed and underwent iterative two-stage testing prior to use. Details will be published elsewhere, in the context of the validation study (see above, explorative objective). Briefly, the FRCL is a grid constructed by a closed-ended list of 13 food categories and relevant subgroups with related, typical add-ons, which represent the major sources of Na and K. Frequency and quantity of daily intake is reported by ticking the number of reference portions (1 to 5+) consumed per meal (breakfast, AM snack, lunch, etc.). For estimation of Na and K intake, a FRCL database was compiled based on the Swiss food composition database [75] and FSVO laboratory data from earlier studies [18, 19]. Additional questions on meal-based discretionary salt use and aspects of eating in the staff canteen were added at the end of the checklist.

Study staff instructed participants about how to complete the FRCL. At time of pick-up, together with urine containers, study staff collected the three checklists and checked them for completeness and inconsistencies. If needed, participants were contacted to verify information prior to data entry in the trial database.

#### 24-h urine collection

Participants collected urine following the WHO/PAHO standard protocol during a previously agreed upon 24 h period [72]. Study staff instructed participants individually on the urine collection procedure. They received a bag carrying two labeled collection bottles (2 L, 3 L) and a urine collection recording sheet. On the day of collection, the first morning urine was discarded (start time) and all urine voided thereafter was collected up until next morning at approximately 24 h after start (finish time). Participants recorded collection start and finish dates and times, missed/spoiled urine collections, and medication use. They were asked to keep the bottles dark and cool until pick-up and transport to the centrally based laboratory.

#### Spot urine collection

Participants collected a timed, midstream urine void near the midpoint of a morning-to-morning 24-h collection period, at around 17 h00 [76]. Study staff instructed each participant on collection procedure and completion of the recording sheet, which asked for the date and actual time of spot-urine collection, the time and kind of last solid and liquid food intake, the type and intensity of physical activities during the four hours prior to voiding, and medication use. These information will be considered when comparing spot- and 24-h urine based Na/NaCl intakes. Participants used a labeled 100 ml screw capped container for spot-urine collection, which they kept refrigerated and dark in a 1 L plastic zip-top bag until pick-up.

Study staff collected all urine containers and recording sheets, checked the latter for completeness, and if needed contacted participants to verify information prior to data entry in the trial database.

#### Laboratory determination of urinary sodium, potassium, creatinine, and iodine concentrations

The [name] medical laboratory collaborated with the FSVO laboratories in central urine analysis in Bern, Switzerland. Study staff delivered 24-h and spot urine containers to the medical laboratory. A technician gravimetrically estimated the individual total 24-h urine collection volume in milliliters assuming a specific weight of one. For both 24-h and spot urine samples five 2 ml aliquots each were prepared. Two aliquots of each sample were analyzed immediately; the remaining aliquots were retained at − 20 °C for later analysis.

The medical laboratory analyzed urinary Na and K concentrations (mmol/L) with an indirect ion selective electrode technique (Roche eLabDoc ISE indirect Na-K-Cl for Gen.2 Global, V9.0). Urinary creatinine (Creat) concentration (μmol/L) was determined by the kinetic Jaffe method (Roche eLabDoc Creatinin Jaffé Gen.2, V17.1). The [name] medical laboratory performed daily internal and external quality controls according to SWISSMEDIC and QUALAB guidelines.

If urinary Na concentration was below detection limit (20 mmol/L), the FSVO laboratories analyzed a retained aliquot using ICP-OES, which is more sensitive than ISE. They further determined urinary I concentration (μg/L) with inductively coupled plasma mass spectrometry using isotope dilution analysis with addition of an I-129 tracer solution and measuring the I-127/I-129 ratio [77] to calculate I concentration according to Adriaens et al. [78]. In each series of Na and I measurements, four samples of the standard reference material 2670a (US National Institute of Standards and Technology) were measured for quality control purposes. All measured values agreed well with the certified Na and I concentrations.

#### Estimation of daily sodium, potassium, and iodine excretion/intake

We standardized urinary measures to a 24-h period by correcting the urinary volume for the reported duration of urine collection. Daily Na and K excretion (mg/24 h) was derived by multiplying urinary concentration (mmol/L) by 24-h volume (L/24 h) and by atomic weights (Na, 23 mg/mmol; K 39.1, mg/mmol). Predicting Na and K intake from urinary excretion without correcting for possible minor losses via sweat or feces has been judged feasible and to have good predictive power [79]. For equivalent daily NaCl intake (g/day), we multiplied Na excretion (mg/24 h) by 2.54. Calculation of daily I intake (μg/24 h or μg/day) accounted for urinary concentration that represents 92% of ingested iodine [80, 81]: urinary concentration (μg/L) / 0.92 × 24 h-volume (L/24 h).

#### Completeness of 24-h urine samples

We accepted collection durations of 24 h +/− 4 h (20-28 h), but rejected urine samples if (i) total volume was below 300 ml, (ii) two or more voidings were missed, and (iii) urinary Creat excretion was above 400 μmol/kg/24 h. After exclusion of unacceptable urine samples, we compared the measured 24-h Creat excretion (μmol/kg/24 h) of remaining samples with sex-specific Swiss reference values [82] to evaluate their quality (adequate, incomplete, or over-collected). We checked plausibility of Creat concentrations of incomplete and over-collected samples, using explanatory information assessed at time of urine collection, about body mass index (BMI) and waist circumference (adiposity/low lean body mass), metabolic disease, intensity of physical activity, and food/protein intake. In a subsequent sensitivity analysis, we compared mean Na and K excretion and NaCl intake of the inadequate and adequate samples, the inadequate and all acceptable samples, and all acceptable samples with those of the adequate samples. We tolerated relative differences of maximum +/− 15% to include all acceptable samples in analysis [83].

#### Blood pressure

Blood pressure (BP) was measured according to the 2013 European guidelines for office BP management [84]. We used new, calibrated OMRON HEM-907 validated automatic BP measuring devices. The device additionally performed heart rate measurement. Participants were seated in the quiet room and at rest for ca. 5 min prior to measurement. Depending on upper arm circumference, a different cuff size (S/M/L) was chosen. At t0 we first performed single BP readings on both arms to determine the arm for all follow-up measurements. If a between-arms difference in systolic BP of > 10 mmHG was identified, the arm with the higher value was taken as reference arm, otherwise we performed measurements on the non-dominant arm. We took three consecutive measurements one minute apart and calculated the mean of the last two readings. Hypertension was defined as systolic BP ≥140 mmHg and/or diastolic BP ≥90 mmHg and/or being on antihypertensive treatment.

#### Anthropometrics

Anthropometric measurements followed a protocol that was adapted from international standard procedures and applied in other surveys in Switzerland [85, 86]. Study staff briefly explained all measures to the participant and asked for approval. Participants wore light clothing and no shoes when body weight and height were measured to the nearest 0.1 kg and 0.1 cm using a digital flat scale (seca 803) and a mobile stadiometer (seca 217). Before entering data into the study database, we subtracted 1.0 kg from the body weight readings in order to account for average weight of garments [85, 87]. Waist circumference was measured with the shirt lifted, halfway between the iliac crest and the lower rib, using an ergonomic circumference measuring tape (seca 201). The measure was taken twice to the nearest 0.1 cm. At a difference of more than 0.5 cm, a third measurement was taken, and the mean of the two closest measurements calculated. In analysis we considered two measures of weight status and related cardio-metabolic risk, BMI, calculated as weight divided by height squared (kg/m2) [88] and the waist to height ratio (WHtR) [89].

### Data management

Study data collection and management was arranged in REDCap (Research Electronic Data Capture), a secure, web-based application designed to support data capture for research studies, hosted at the Clinical Trials Unit (CTU), University of Bern [90].

For urinary and food laboratory analysis data, partners defined a common database structure and transfer protocol between the laboratories’ information and management systems and the trial’s database management system. At time of data import into REDCap, we checked for keyboarding errors, completeness and consistency of data, and made corrections in all systems, if applicable. CTU and study staff verified all imports in REDCap.

A trained research assistant entered the health questionnaire (paper version), FRCL, urinary collection recording sheets, and catering surveys in REDCap. Data entry was double checked by study staff.

### Statistical analysis

For baseline analysis, continuous variables were summarized descriptively using mean and 95% confidence interval (CI) or median and range depending on sample size and type of variable. For categorical variables, we used frequency and percentage. Variables were summarized overall, separately for intervention and control group, and by sex. At cluster level, Na, K, and NaCl levels of menu components were calculated weighted for sales numbers. At participant level, comparisons between groups were performed using t-tests for continuous variables, and chi-squared tests or Fisher’s exact tests for categorical variables depending on the expected number per cell. We applied two-tailed tests with significance level 0.05 for all analyses. Because baseline analysis was exploratory and hypothesis generating, no adjustment for multiple testing was done.

We used and will use baseline data to explore factors related to salt intake and evaluation of questionnaires. Statistical analyses are described in the respective articles [71, 91]. Future analysis will include application of a linear mixed model with organization as random effect to assess the change in primary outcome from t0 to t12. All analyses are run using R 3.3.2 [92].

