### Study design

Healthful & Tasty is a combined educational and environmental trial in the Swiss workplace to promote health by lowering Na intake in a nutritionally balanced, healthy diet. Health promotion activities in the workplace are typically driven by legal responsibilities for occupational health and safety in Switzerland. Nutrition education and structural measures in catering facilities are not standard components in the national program Friendly Work Space [35]. Moreover, many organizations with staff canteens outsource catering and related food health responsibility to large catering firms, which offer labeled, nutritious menus. The trial recruited organizations and their employees, but catering firms had to agree to the intervention as well. We established a cluster randomized controlled trial (cRCT), received ethical approval by Swissethics, and registered the trial in September 2014.

Considering experiences from our own studies in communal catering [18, 19, 36, 37] and reports in the literature [38–41], and in agreement with the NRP69 scientific steering committee we prepared for having to adjust the study design if recruitment with randomization and matching at cluster level proved to be infeasible within six months (Table 1).

**Table 1 Tab1:** Study design options of the “Healthful & Tasty: Sure!” workplace trial

	Experimental study design	Alternative quasi-experimental study design
Design	Cluster randomized controlled trial	Cluster nonrandomized single arm trial with calibration arm
Blinding	No	No
Pair-wise matching	Yes	No
Sample size estimation (power calculation)	Assumptions: baseline mean 24-h urine sodium excretion of 180 mmol [16, 17, 42], standard deviation of 65, intra-cluster correlation coefficient of 0.05, 16 clusters and drop-out rate of 25%. Objective: detect between-group difference of at least 15% (i.e. 27 mmol) at trial end with alpha 0.05 and 80% power.	Assumptions: baseline mean 24-h urine sodium excretion of 180 mmol [16, 17, 42], standard deviation of 65, intra-cluster correlation coefficient of 0.05, and drop-out rate of 10%. Objective: detect sodium intake reduction by 15% (i.e. 27 mmol) until trial end with alpha 0.05 and 80% power.

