#### Cluster level

A total of 389 organizations with catering facilities were assessed for eligibility. Of these, 146 were not reached, 186 declined to participate, and 49 did not meet the inclusion criteria. Finally, eight organizations were included in the trial, seven participating in the intervention arm and one in the control arm.

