#### Participant level

Of 5794 eligible employees (5394 intervention, 400 control), 145 employees (132 intervention, 13 control) met the inclusion criteria and provided written consent. Baseline analysis included 141 participants (128 intervention, 13 control) with adequate 24-h urine samples.

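### Baseline tests of intervention versus control ignore clustering: at the plan's ICC of 0.05, the nominal 5% t-test has a true level of about 12%

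*Protocol article*

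**What the plan says.** The Statistical analysis section of the protocol article describes the baseline analysis. Variables are summarized overall, by arm and by sex, with means and 95% CIs for continuous variables where suitable. For individual participants it then reports that "comparisons between groups were performed using t-tests for continuous variables". Categorical variables get a chi-squared or a Fisher test, chosen by the expected cell counts. The level is fixed too: "We applied two-tailed tests with significance level 0.05 for all analyses". The exploratory status of the baseline analysis is given as the reason for not adjusting for multiple testing. Clustering is not mentioned for these tests or intervals.

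Elsewhere the document does allow for clustering. Table 1 (Study design) assumes an "intra-cluster correlation coefficient of 0.05" for 24-h urinary sodium. The last paragraph of Statistical analysis plans a mixed model with a random organization term for the change in the primary outcome.

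On structure, the Participation section reports that "eight organizations were included in the trial, seven participating in the intervention arm and one in the control arm". At participant level: "Baseline analysis included 141 participants (128 intervention, 13 control) with adequate 24-h urine samples".

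**The concern.** Employees of one organization share a canteen, a sector and a workforce profile, so their values are correlated. A t-test or chi-squared test on individuals assumes that they are not. For intervention versus control the problem is acute because the whole control group is one organization. Any peculiarity of that organization is read as a difference between arms, and more control participants from the same site would not cure this.

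The baseline comparisons therefore do not have the stated 5% error rate. Some differences flagged between the arms would be ordinary differences between organizations. The 95% CIs of means in Table 3 have the same weakness if they were computed in the usual way.

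**Working it through.** **Inputs.** Two-sided level 0.05 (Statistical analysis); ICC 0.05 for urinary sodium (Table 1); 128 participants in 7 intervention organizations and 13 in 1 control organization (Participation). Cluster sizes are not given, so equal intervention clusters are assumed: 128/7 = 18.3 each.

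**Stated figure.** With ICC = 0 both design effects are 1, the variance ratio is 1, and the level is the stated 5% (simulation, pooled t-test: 5.0%).

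**t-test at ICC 0.05.**
- Design effect, intervention: 1 + (18.29 − 1) × 0.05 = 1.864.
- Design effect, control: 1 + (13 − 1) × 0.05 = 1.60.
- True variance of the difference, in units of the outcome variance: 1.864/128 + 1.60/13 = 0.01457 + 0.12308 = 0.1376.
- Naive variance: 1/128 + 1/13 = 0.0847.
- Ratio R = 0.1376/0.0847 = 1.62; the true SE is √1.62 = 1.27 times the naive SE.
- True level: 2 × [1 − Φ(1.96/1.27)] = 0.124.

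A simulation of 60,000 trials gives 12.5% (pooled) and 12.4% (Welch) with equal clusters. With one assumed set of unequal clusters it gives 12.8% and 12.6%.

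**Range over the ICC (same formula).**

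| ICC | R | True level |
|---|---|---|
| 0.01 | 1.12 | 6.5% |
| 0.02 | 1.25 | 8.0% |
| 0.05 | 1.62 | 12.4% |
| 0.10 | 2.25 | 19.1% |

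**Categorical variables.** The expected control count is (row total) × 13/141. For non-Swiss nationality it is 22 × 13/141 = 2.0; for secondary education 35 × 13/141 = 3.2; for 0–1 lunches per week 30 × 13/141 = 2.8. Under the usual rule of switching below 5 (an assumption, since the article gives no cut-off), every categorical variable in Table 3 except sex would go to Fisher's test. Beta-binomial simulation at ICC 0.05, prevalence 0.25 and 0.50:
- Fisher: 9.0% and 11.3%.
- Uncorrected chi-squared: 11.4% and 13.0%.
- Yates-corrected chi-squared: 6.1% and 8.0%.

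**Comparison by sex.** With the sexes evenly mixed within organizations, simulation at ICC 0.05 gives 5.0%. Letting the share of women vary from 19% to 70% across organizations (the employee range in Table 2, values between assumed) gives 5.9%.

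**Intervals for means.**
- Intervention arm: naive width / true width = 1/√1.864 = 0.73, so about 27% too narrow.
- Overall: 141/8 = 17.6 per organization; design effect 1 + 16.6 × 0.05 = 1.83; 1 − 1/√1.83 = 0.26, so about 26% too narrow.

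**Were the printed intervals adjusted?** In Table 3 the intervention-arm age interval is 42.2 to 46, a half-width of 1.9. The age bands suggest an SD of about 11, so the naive half-width is about 1.98 × 11/√128 = 1.9. With a design effect of 1.86 it would be about 1.9 × 1.36 = 2.6. The printed interval matches the unadjusted calculation.

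**The case against.** The best defence is that little rests on these tests. They are declared exploratory, Table 3 prints no p-values, and the text around Tables 2 and 3 claims no significant difference. The effectiveness analysis is a separate model that includes organization. All of this stands and limits the weight of the point. It does not restore the stated level, because the exploratory label is used only to waive multiplicity adjustment.

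A second defence is that the null is a choice. If the question is only whether these particular enrolled groups differ, a difference between organizations is itself the confounder of interest, and the test is not inflated in this way. That is fair. But a hypothesis-generating analysis looks beyond the enrolled groups, and the plan itself treats organizations as random in its main model.

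Third, the ICC is stated for urinary sodium only. Other baseline variables may have smaller or larger values, which is why a range is shown.

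Stronger readings are tempting, and the document does not support them:
- A reader might infer that every baseline test runs at 12%. Fisher tests are inflated less, and comparisons by sex hardly at all.
- A reader might infer that baseline p-values will steer covariate choice or the primary result. No section says that covariates are chosen this way, and the primary model has its own organization term.
- A reader might infer that the related work on factors linked to salt intake is affected. Its methods are described in separate articles that are not shown.

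**Conclusion.** The point holds for baseline comparisons of intervention with control and for the 95% CIs of means. At the plan's ICC the t-test has a true level of about 12% instead of 5%; at ICC 0.01 to 0.10 the range is about 6.5% to 19%. Fisher's test, likely for most categorical variables, runs at about 9 to 11% at ICC 0.05. The naive interval for the intervention-arm mean is about 27% too narrow.

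These figures assume roughly equal intervention clusters, organizations regarded as draws from a wider population, and an ICC borrowed from urinary sodium. That the printed intervals are unadjusted is an inference from one variable, age, whose own ICC is unknown; with an age ICC near zero, an adjusted interval would look the same. The damage is limited to exploratory baseline inference. The planned test of the change in sodium excretion is not affected by this point.

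**What to change.** Omit p-values for intervention versus control at baseline and report descriptives only, as Tables 2 and 3 already do. Adding a random organization effect to the arm comparison is not a substitute: with one control organization, arm and organization cannot be separated.

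Give cluster-adjusted 95% CIs for the overall and intervention-arm means. State beside the control-arm interval that it reflects variation among employees of one organization only, since one cluster cannot support an adjusted interval. Comparisons by sex can stay as they are; a mixed model would change them very little.

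The computing effort is small and uses existing data. The cost is that some baseline differences lose their p-value and the intervals become wider. The Baseline information section says that the full baseline results are published elsewhere, so tests already in print could be changed only by a correction; the fix is simplest for reports still to come.
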